#### Women/mothers

Reproductive health as assessed by fecundability, pregnancy loss and live birth rates, and sexual function based on Female Sexual Function Index-19.^36^Pregnancy outcomes include pain, obstetric and delivery complications.Health behaviours assessed by dietary practice (6P tool,^30^ 4-day food diary, Food Frequency Questionnaire,^37^ Three Factor Eating Questionnaire,^38^ alcohol and supplement intake), smoking exposure, physical activity and sedentary behaviours (International Physical Activity Questionnaire,^39 40^ Sedentary Behaviour Questionnaire,^41^ accelerometer), and sleep (Pittsburgh Sleep Quality Index,^42^ digital tracker).Metabolic profile, including weight status, body fat distribution, blood pressure, lipid and glycaemic measures.Gut microbiome profile assessed by stool sample.Nutrient status based on diet, blood and breast milk composition (breast milk will be collected at five time points through the first year postdelivery).Ocular health as assessed by retinal vessel calibre characteristics.

#### Offspring

Anthropometry and growth assessed by antenatal serial ultrasound scans, infant weight, length and head circumference.Neonatal complications such as hypoglycaemia and admission to neonatal care facilities; infant health and well-being, and skin biopsy for a subset of infants with eczema.Infant feeding assessed by breastfeeding behaviours, time of weaning, nutrition milestone, dietary intake and eating behaviours.

#### Partners

Physical and metabolic health assessed by weight, BMI and body fat distribution.Health behaviours assessed by smoking exposure, alcohol intake, meal pattern, stress level, physical activity and sedentary behaviours.

Programme effectiveness will be evaluated based on women’s quality of life, healthcare utilisation and participant feedback surveys. Blood, cord blood, stool, urine, saliva, placenta and breast milk samples will be stored for analyses on biochemical, micronutrient, metabolomic, genomic, epigenetic, immunological and molecular profiles.

### Planned analyses

Continuous variables will be presented as means and SD, or medians and 25th–75th centiles, as appropriate. Categorical variables will be presented as numbers and percentages. The pregnancy rate will be determined by the number of women who became pregnant (defined as stated previously) divided by the total number of women who completed the 1-year follow-up during the preconception phase. The time to pregnancy (TTP) will be estimated by the number of menstrual cycles required to achieve pregnancy over 1 year of follow-up. We will use the discrete-time proportional hazards model, which analyses TTP as a discrete scale based on the number of menstrual cycles, to estimate the fecundability ratio (FR) and the 95% CI,^43 44^ accounting for left truncation and right censoring. For the other two coprimary outcomes, a linear mixed effects model will be used to examine changes in means between the baseline and follow-up metabolic markers and EPDS scores, with adjustment for baseline potential confounders (including partner’s characteristics) and duration of the intervention received. In addition to the pre–post comparison of outcomes stated above, differences in pregnancy and birth outcomes will also be compared with a similar observational cohort in Singapore called Singapore PREconception Study of long-Term maternal and child Outcomes (S-PRESTO),^45^ using multiple linear or logistic regression models, adjusting for potential confounders. These confounders, such as age, ethnicity and education, will be determined from literature review, directed acyclic graph and/or observed statistically significant associations with exposures and outcomes.

We will impute missing data using multiple imputation analyses by chained equations.^46^ The number of imputations will be determined based on a percentage of missing values,^47^ and the results of total imputations will be pooled using Rubin’s rule.^48^ To determine whether the imputation of the missing data may have affected the results, we will perform sensitivity analyses on participants with a complete set of data.

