### Participants and recruitment

Potential participants from the public or KKH (patients/staff) or referred from other healthcare institutes who fulfil the inclusion criteria will be invited to participate in the HELMS study. KKH houses the largest Obstetrics and Gynaecology department in Singapore, managing approximately 12 000 deliveries a year with patients made up of a wide sociodemographic spectrum. Invitation letters, emails, messages, webpages, brochures and posters will be used for advertising. Interested women can contact the study team by email or phone.

Inclusion criteria include (1) a woman who plans to conceive in the next 12 months; (2) BMI 25–40 kg/m^2^; (3) age 21–40 years; (4) Chinese, Malay, Indian ethnicity or any combination of these three ethnic groups; (5) intending to reside in Singapore for the next 4 years; (5) can access the Internet through any digital platform and (6) can provide written informed consent. Exclusion criteria include (1) currently pregnant; (2) difficulty in understanding the English language; (3) known type 1 or type 2 diabetes; (4) being on anticonvulsant medication, oral steroid, contraception or fertility medication in the past 1 month; (5) on HIV or Hepatitis B or C medication in the past 1 month. If a woman is pregnant within 1 month from the baseline visit, they will be censored from the analyses. If a woman has a pregnancy loss and wishes to rejoin the study, she will be recharacterised at the preconception baseline visit at least 1 month after a negative urine pregnancy test and will receive intervention as before.

Women who suffer from a miscarriage or termination event, experience multiple pregnancies, with fetal congenital anomalies, cannot comply with the study protocol or wish to discontinue their participation will be withdrawn from the study.

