### Outcomes and assessments

The primary outcome is the pregnancy rate in overweight and obese women trying to conceive within 1 year of baseline assessment. It is defined by a positive urine pregnancy test, followed by ultrasound confirmation of an intrauterine gestational sac after 6 weeks of amenorrhoea. If an ultrasound scan is not available or inconclusive, the diagnosis of pregnancy will be made clinically. A successful conception is one of the most important clinical outcomes, and it represents the culmination of improved metabolic and mental health, leading to optimised gametogenesis.

Coprimary outcomes include maternal metabolic health and mental health status in each phase, with 18 months postdelivery serving as the principal endpoint. Maternal metabolic health is assessed by metabolic syndrome criteria. Mental health is evaluated using the Edinburgh Postnatal Depression Scale (EPDS).^35^

Other key outcomes include:

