### Sample size calculation

Based on the S-PRESTO study,^45^ which is an observational cohort recruited from preconception and followed up through postpartum periods, preconception overweight or obese women (BMI ≥25 kg/m^2^) had a 38% pregnancy rate, while those with normal weight (BMI 18.5–24.9) had 47% pregnancy rate. Among overweight and obese women, those with healthy metabolic profiles characterised by absence of the metabolic syndrome or insulin resistance had a 52% pregnancy rate. We anticipated that HELMS intervention will improve overweight or obese women’s pregnancy rate from 38% to 50% within 12 months of trying. Using a two-sided α level of 5% and a power of at least 90%, 400 participants are needed in the preconception phase, leading to 200 pregnancies. Considering a 20% drop-out rate, 500 participants are required for recruitment. We estimated that 15% of women will experience pregnancy loss and another 10% drop-out, leaving 150 dyad pairs to be followed.

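### The completer denominator for the primary pregnancy rate drops women who leave without conceiving but keeps women who conceive, so drop-out after baseline that is unrelated to fertility overstates the 12-month pregnancy probability

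*Protocol article*

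**What the plan says.** Under Outcomes and assessments, the protocol article states: "The primary outcome is the pregnancy rate in overweight and obese women trying to conceive within 1 year of baseline assessment". The Planned analyses section then fixes the calculation: "The pregnancy rate will be determined by the number of women who became pregnant (defined as stated previously") is the numerator, "divided by the total number of women who completed the 1-year follow-up during the preconception phase". The same paragraph plans a discrete-time model of time to pregnancy, "accounting for left truncation and right censoring", to estimate a fecundability ratio. It also plans multiple imputation, in general terms.

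Three other places bear on who counts:

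- Trial design and setting: only women who have not conceived have a 12-month exit visit. Women who conceive move to the pregnancy visits.
- Participants and recruitment: women who "cannot comply with the study protocol or wish to discontinue their participation will be withdrawn from the study". The same section removes from the analyses women who are pregnant within 1 month of the baseline visit.
- Sample size calculation: overweight or obese women in the S-PRESTO cohort "had a 38% pregnancy rate", and the intervention is expected to raise the "pregnancy rate from 38% to 50% within 12 months of trying". The plan needs 400 women, giving 200 pregnancies. "Considering a 20% drop-out rate, 500 participants are required for recruitment".

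**The concern.** Whether a woman enters the denominator depends on the outcome. A conception after the first month secures her place whenever it occurs. Without a conception she must stay the full year. A woman who leaves early has contributed months of trying without success, and the rule discards those months.

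The first-named primary outcome, on which the sample size rests, is affected. With drop-out unrelated to fertility, the error moves the reported rate upward, towards the 50% target. A single-arm trial has no concurrent control group in which the same error would occur.

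Nothing else in the article repairs it. The censoring belongs to the model for the fecundability ratio, not to the rate. The imputation statement is not linked to the rate, whose definition already excludes the women with missing outcomes.

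**Working it through.** **Inputs.** From Sample size calculation: 500 recruited, 20% drop-out, 400 analysed, reference 38%, target 50%. From Planned analyses: the denominator rule. From Participants and recruitment: the one-month rule. The timing of drop-out is not given, so it is assumed and varied.

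**The plan's own figures.** 400 / (1 − 0.20) = 500, and 400 × 0.50 = 200. Both reproduce. They also show that pregnant women are meant to be inside the 400.

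**Rule tested.** Rate = pregnant / (pregnant + non-pregnant at 12 months). Drop-out happens only before pregnancy and totals 20%, so with 500 enrolled the denominator is 400. The true 12-month probability is set at 38%.

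**Constant hazards, drop-out independent of fertility.**

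- Conception hazard: λ = −ln(1 − 0.38) = 0.478 per year.
- Drop-out hazard μ solves μ/(λ+μ) × (1 − e^−(λ+μ)) = 0.20, giving μ = 0.286.
- Pregnant before drop-out: λ/(λ+μ) × (1 − e^−(λ+μ)) = 0.334, or 167 of 500.
- Non-pregnant at 12 months: 500 − 167 − 100 = 233.
- Protocol rate: 167/400 = 41.8%, which is 3.8 points above the truth.

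**All drop-out at one time t (months), unrelated to fertility.** With S = e^(−λt/12), the fraction pregnant is (1 − S) + (S − 0.20)(1 − e^(−λ(1 − t/12))). Dividing by 0.80 gives the protocol rate.

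| Drop-out at | Pregnant of 500 | Protocol rate |
|---|---|---|
| baseline | 152 | 38.0% |
| month 3 | 160 | 40.0% |
| month 6 | 169 | 42.2% |
| month 9 | 179 | 44.7% |
| just before month 12 | 190 | 47.5% |

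The last row is the extreme. The same 190/400 arises if every woman who leaves, at whatever time, is one who would not have conceived.

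**With first-month conceptions removed** (reading the one-month rule as removal from numerator and denominator).

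- Constant hazards, 20% drop-out: about 19.3 conceptions fall in month 1. (167.1 − 19.3)/(400 − 19.3) = 147.8/380.7 = 38.8%.
- No drop-out: about 19.5 fall in month 1. (190 − 19.5)/(500 − 19.5) = 170.5/480.5 = 35.5%.
- Difference due to the denominator: 38.8 − 35.5 = 3.3 points.
- Extreme case: 170.5/(400 − 19.5) = 44.8%.

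**What the alternatives return for a true 38%** (one-month rule left aside).

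- Censoring at drop-out, drop-out independent of fertility: 38.0%.
- Lost women counted as not pregnant, constant hazards: 167/500 = 33.4%, which is conservative.
- Censoring at drop-out, all drop-outs non-conceivers leaving evenly over the year: about 43.0%. Censoring alone does not cure informative drop-out.
- Lost women counted as not pregnant, in that same case: 190/500 = 38.0%.

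**The case against.** **Size.** The bias need not be large, or even positive. It is zero if all drop-out is at baseline and 2.0 points if all is at month 3, and it could be offset if leavers were more fertile than stayers. All of this stands. The definition gives an upward bias under drop-out that is unrelated to fertility and occurs after baseline, not under every pattern.

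**The one-month rule.** It takes the earliest conceptions out of the numerator, so the constant-hazard rate comes out at 38.8%, close to the 38% reference. That stands too. But the two effects merely oppose each other: with that rule and no drop-out the figure would be 35.5%, and the denominator still adds about 3.3 points.

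**The benchmark.** The article does not say how the S-PRESTO 38% was calculated. If it is also a completer rate with similar drop-out, part of the bias cancels in the comparison. The reported HELMS rate would still overstate the 12-month probability.

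**Purpose.** The Discussion presents the trial as seeking preliminary evidence and concedes the limits of a single arm. It does not mention this limit, which is avoidable.

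Three stronger readings are tempting but not supported:

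- A reader might infer that women who conceive never complete the year and so fall outside the denominator, making the ratio meaningless. The sample size section rules this out, because its 200 pregnancies are among the 400 women.
- A reader might infer that the plan contradicts itself by censoring drop-outs in one analysis and excluding them in another. A crude proportion and a fecundability ratio are different quantities, and planning both is not a contradiction.
- A reader might attach an inflated false-positive rate to the trial. The article names no test of the rate against 38%, and the construction of the 38% is unknown, so no such rate can be given.

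**Conclusion.** The defect is real and lies in the stated definition, so it is not a detail left to another document. For a true 38% and the plan's 20% drop-out, the overstatement runs from 0 points (all drop-out at baseline) through 3.8 points (constant hazards) to 9.5 points (47.5 − 38, the extreme), if the one-month rule is left aside. With that rule applied, the constant-hazard overstatement is about 3.3 points. The planned gain is 12 points.

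The constant-hazard and timed figures assume drop-out independent of fertility. The upper end needs either very late drop-out or drop-out made up entirely of women who would not have conceived. How far a comparison with the 38% is affected cannot be settled from the article.

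**What to change.** Replace the completer denominator with the 12-month cumulative probability of pregnancy, from a life table or derived from the discrete-time model already planned. All eligible enrolled women enter the risk set, and non-pregnant drop-outs are censored at last contact. Apply the one-month rule in the same way throughout, for example as delayed entry at month 1.

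Because censoring does not correct informative drop-out, add a sensitivity analysis that counts every lost woman as not pregnant. Compute the S-PRESTO benchmark by the same rule, including the one-month rule.

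The cost is about one sentence of analysis wording and a headline rate that may be a few points less favourable. No new data need be collected in HELMS.

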## Methods and analysis

### Trial design and setting

This study represents a model of implementation to demonstrate the value of adopting a life-course approach and integrated care to maternal–child health. It is conceptualised as a single-arm trial, with a targeted intervention implemented in a group of women living with obesity who are trying to conceive within 1 year after recruitment. The longitudinal intervention will be performed from preconception, throughout pregnancy until 18 months postpartum in the KK Women’s and Children’s Hospital (KKH), Singapore. The protocol is written following the SPIRIT (Standard Protocol Items: Recommendations for Interventional Trials) guidelines. Written informed consent will be obtained from all participants at the recruitment.

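### The trial is sized on raising the 12-month pregnancy rate from 38% to 50%, but no planned analysis clearly estimates or tests that difference

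*Protocol article*

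**What the plan says.** Outcomes and assessments states: "The primary outcome is the pregnancy rate in overweight and obese women trying to conceive within 1 year of baseline assessment". Two coprimary outcomes, metabolic health and mental health, follow.

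Sample size calculation takes 38% from overweight or obese women in S-PRESTO and expects the intervention to move the "pregnancy rate from 38% to 50% within 12 months of trying". With two-sided 5% alpha and at least 90% power it asks for 400 women, or 500 after allowing for 20% drop-out.

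Trial design and setting says of the study: "It is conceptualised as a single-arm trial". Intervention overview confirms that every participant receives the intervention.

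Planned analyses then offers, for conception:
- a rate, with the number pregnant "divided by the total number of women who completed the 1-year follow-up during the preconception phase";
- a discrete-time proportional hazards model of time to pregnancy in menstrual cycles, "to estimate the fecundability ratio (FR) and the 95% CI".

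The same section adds that "differences in pregnancy and birth outcomes will also be compared with a similar observational cohort in Singapore", namely S-PRESTO, by linear or logistic regression with adjustment. Confounders may come from literature, a directed acyclic graph and/or "observed statistically significant associations with exposures and outcomes".

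The list of maternal outcomes says: "Pregnancy outcomes include pain, obstetric and delivery complications". It puts fecundability under a different item, reproductive health. The Abstract lists pregnancy outcomes as secondary and the pregnancy rate as primary.

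**The concern.** A sample size with an alpha, a power and two rates presupposes a test of one rate against the other. The analysis section should contain that test, and on a plain reading it does not. The proportion is descriptive. A fecundability ratio is a ratio of per-cycle conception probabilities between two groups; here everyone is exposed to the intervention and no other contrast is named. The one comparison with an outside group is described in a term that the article otherwise reserves for secondary outcomes.

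At stake is the inference on the primary outcome. If the comparator and the test are not settled, they can be chosen after the pregnancy rate is known, and the possible choices differ widely in power and in type I error.

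**Working it through.** **1. Which stated analysis could carry the 38% versus 50% comparison?**

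- *Proportion among completers.* No comparator or test is attached.
- *Discrete-time model.* No exposure is named. Within one arm it can give ratios for, say, obese versus overweight women. The only within-arm contrast hypothesised (Goals and aims) is that one, and it concerns metabolic and mental health, not conception.
- *Pre–post comparison.* Women who are pregnant at entry are excluded, so the pregnancy rate has no baseline value.
- *S-PRESTO comparison.* It covers pregnancy and birth outcomes. The Abstract and the maternal outcome list use pregnancy outcomes for something separate from the pregnancy rate and from fecundability. The Discussion describes comparison with the historical cohort only as a potential.

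None of the four clearly carries it.

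**2. The plan's own figure**

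Inputs from Sample size calculation: p0 = 0.38, p1 = 0.50, two-sided alpha 0.05, power 0.90; difference d = 0.12.

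- One sample against a fixed 38%: n = [1.960·√(0.38·0.62) + 1.282·√(0.50·0.50)]² / 0.12² = (0.951 + 0.641)² / 0.0144, about 177.
- Two samples, with mean rate 0.44: n = [1.960·√(2·0.44·0.56) + 1.282·√(0.2356 + 0.25)]² / 0.0144 = (1.376 + 0.893)² / 0.0144, about 358 per group (374 with continuity correction).

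Neither formula gives 400. Both meet the condition of at least 90% power at 400: 99.8% for one sample, and 92.9% for two groups of 400. So 400 is not wrong, but it does not show which test was meant. The drop-out step reproduces: 400 / 0.80 = 500.

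**3. The targeted effect as a fecundability ratio**

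Assume a constant per-cycle probability and 12 cycles.

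- At 38%: 1 − 0.62^(1/12) = 0.0391.
- At 50%: 1 − 0.50^(1/12) = 0.0561.
- Ratio: 0.0561 / 0.0391 = 1.44 (also 1.44 with 13 cycles).

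**4. Power of a comparison with S-PRESTO**

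The article does not give the number m of overweight or obese S-PRESTO women, so a range is assumed. With 400 HELMS women and p̄ the pooled rate:

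power = Φ{[0.12 − 1.960·√(p̄(1−p̄)(1/400 + 1/m))] / √(0.25/400 + 0.2356/m)}

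For m = 200: p̄ = (200 + 76)/600 = 0.46, and (0.12 − 0.0846) / 0.0425 = 0.834, which gives 79.8%.

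| Assumed S-PRESTO women | Unadjusted power |
|---|---|
| 100 | 57.7% |
| 200 | 79.8% |
| 300 | 88.7% |
| 400 | 92.9% |

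At least 324 are needed for 90%.

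**5. Type I error if 38% is treated as fixed**

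If 38% is itself an estimate from m women, the 1.960 threshold shrinks to 1.960·√[(1/400)/(1/400 + 1/m)].

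- m = 200: 1.960 × 0.577 = 1.13, a two-sided error of about 26%.
- m = 400: 1.960 × 0.707 = 1.39, a two-sided error of about 17%.

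**The case against.** The best defence is that the S-PRESTO sentence can be read broadly. Pregnant or not at 12 months is a natural logistic outcome, the 38% comes from the same cohort, and the maternal outcome list says what pregnancy outcomes include, which is not a closed definition. That reading is not excluded. The article's own usage in the Abstract and the outcome list goes against it, so the text is at best ambiguous on its primary outcome.

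A second defence is that a condensed article may leave the exposure in a model to a fuller document. That would hold if the article were silent. Here it states the analysis of the primary outcome, and what it states does not match the hypothesis used for the sample size.

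Several stronger readings are tempting, and the documents do not support them:

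- *That a fecundability ratio is impossible in a single arm.* It needs a contrast, not a second arm. Ratios between baseline groups are legitimate; they just do not test the intervention.
- *That the trial cannot answer its question.* The coprimary outcomes have a stated longitudinal model, S-PRESTO data are already to be used, and the article discloses the limits of a single arm and aims for preliminary evidence.
- *That the 38% group lacked HELMS's diabetes and fertility-drug exclusions.* S-PRESTO's eligibility criteria are not given. Only its BMI group, 25 or more with no stated upper limit, is visible.
- *That the logistic models ignore censoring.* A 12-month yes/no outcome among women with complete follow-up has none to ignore.
- *That selecting confounders by significance invalidates the interval.* It is one option under an and/or, and its effect cannot be sized from the documents.

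**Conclusion.** The point stands as a mismatch between the sample-size hypothesis and the stated analysis of the pregnancy rate. Followed as written, and on the article's own use of pregnancy outcomes, the plan yields a completer proportion and a ratio unrelated to the intervention, and no estimate of the 38% to 50% effect.

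The consequence is an unresolved choice of test. Power at 400 HELMS women runs from 99.8% with a fixed 38% down to about 80% or 58% against 200 or 100 S-PRESTO women, and the fixed-38% route carries a type I error of about 17% to 26% if that figure came from 400 to 200 women. These figures assume true rates of 38% and 50%, no adjustment, and S-PRESTO numbers that the article does not give. The fecundability ratio of 1.44 also assumes a constant per-cycle probability. The point concerns the pregnancy rate only, not the two coprimary outcomes.

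**What to change.** - State in Planned analyses that the primary outcome is part of the S-PRESTO comparison. Make cohort the exposure: HELMS versus S-PRESTO women restricted to HELMS eligibility as far as the data allow, including BMI 25–40, with the same time origin and the same pregnancy definition.
- If S-PRESTO holds cycle-level time to pregnancy, which the article does not show, use the discrete-time model already planned with cohort as the exposure. Otherwise use an adjusted 12-month comparison. Report the adjusted fecundability ratio and/or the standardised 12-month risk difference.
- Fix the confounders in advance from the literature and the directed acyclic graph, and drop selection by observed significance.
- Give the number of eligible S-PRESTO women and restate power for this comparison.
- If a one-sample test against 38% is preferred, say so, justify the 38% and allow for its uncertainty.

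This changes the analysis wording and the power statement, not enrolment. The cost is a wider interval than a fixed 38% would give and possibly a stated power below 90%: an unadjusted comparison needs at least 324 S-PRESTO women to reach it.

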### Goals and aims

We envision an integrated life-course approach with a continuum of care that encompasses preconception preparation, pregnancy optimisation, along with postpartum synchronisation of maternal–child health services in the first 18 months of life. Connecting the preconception, pregnancy and postpartum journeys will achieve synergism in producing greater behavioural change and beneficial outcomes not only for women, but also for the child and family.^19^ Therefore, the goal of Healthy Early Life Moments in Singapore (HELMS) is to develop and implement a life-course model of care (MOC) starting from preconception to pregnancy and postpartum phases, to achieve optimal metabolic and mental health for both mother and child. This MOC focuses on preventive healthcare, a time where the cost-effectiveness of the intervention is likely to be maximum,^28^ and represents the clinical translation of early developmental programming based on the Developmental Origins of Health and Disease paradigm.^20^

In this study, the overarching aim is to examine whether an integrated intervention beginning preconceptionally and continuing throughout the pregnancy and postpartum phases can improve the metabolic and mental health of women living with obesity, as well as optimise offspring growth and development. At each life-course phase, the study addresses specific hypotheses. We hypothesise that the HELMS MOC lifestyle interventions will promote the metabolic and mental health of overweight and obese women, and thus optimise (1) reproductive outcomes during preconception, (2) obstetric outcomes during pregnancy and (3) postpartum physical and mental well-being, and healthy feeding habits and growth during infancy. We also hypothesise that greater improvements in metabolic and mental health will be observed in obese women with obesity than in those who are overweight. An overview of the study framework is shown in figure 1.

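### Per-pregnancy comparison with S-PRESTO selects on conception, which the intervention is expected to change; on the planning figures 24% of HELMS pregnancies would be extra conceptions, and the resulting bias has uncertain direction and size

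*Protocol article*

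**What the plan says.** Planned analyses adds an external comparison to the pre–post analyses: "differences in pregnancy and birth outcomes will also be compared with a similar observational cohort in Singapore", namely S-PRESTO. The method is multiple linear or logistic regression with adjustment for confounders. Age, ethnicity and education are given as examples, and the final set is to come from the literature, a directed acyclic graph and/or observed associations.

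Outcomes and assessments lists pain and complications of pregnancy and delivery as the pregnancy outcomes for mothers, and growth on antenatal scans and neonatal complications for offspring. Pregnancy loss and live birth rates appear separately, under reproductive health.

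Goals and aims ties these outcomes to the intervention: "We hypothesise that the HELMS MOC lifestyle interventions will promote the metabolic and mental health of overweight and obese women, and thus optimise" reproductive, obstetric and postpartum outcomes. Sample size calculation states the expected effect on conception: "We anticipated that HELMS intervention will improve overweight or obese women’s pregnancy rate from 38% to 50% within 12 months of trying". It also reports that, among overweight and obese S-PRESTO women, "those with healthy metabolic profiles characterised by absence of the metabolic syndrome or insulin resistance had a 52% pregnancy rate".

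**The concern.** The intervention starts before conception, and conception is the primary outcome. A regression of obstetric or neonatal outcomes on cohort can use only women who conceived, so its analysis set is defined by an event that follows the start of the intervention and that the intervention is meant to change. Even if S-PRESTO women were identical at baseline and follow-up were complete, the pregnant S-PRESTO women would not be the counterparts of all the pregnant HELMS women.

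Adjustment for age, ethnicity and education does not deal with this. The limitations acknowledged in the article (placebo effect, natural history, regression to the mean, generalisability) do not mention it. Obstetric outcomes are a stated hypothesis and have no preconception value for a pre–post comparison, so the S-PRESTO contrast is the only comparative analysis of them in Planned analyses. Without a caveat, a per-pregnancy difference in either direction could be read as benefit or harm.

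**Working it through.** **Inputs from Sample size calculation.** Pregnancy rate 38% in S-PRESTO women with BMI of 25 or more; 50% expected in HELMS; 52% in metabolically healthy overweight or obese S-PRESTO women; "400 participants are needed in the preconception phase, leading to 200 pregnancies".

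**The plan's own figures.** 400 × 0.50 = 200 pregnancies, 400/(1 − 0.20) = 500 recruited and 200 × (1 − 0.25) = 150 dyads all reproduce. The 400 is not the minimum from the usual formulas (177 for one sample against a fixed 38%; 358 per group for two samples). It does meet the stated power of at least 90% (99.8% for one sample; 92.9% for 400 against 400). Nothing below depends on this.

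**Share of extra conceptions.** (p1 − p0)/p1 = (0.50 − 0.38)/0.50 = 0.24, or 0.24 × 200 = 48 pregnancies. This is exact if the intervention prevents no conceptions, and a minimum otherwise. It moves with the inputs:

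| Untreated rate in HELMS women | HELMS rate reached | Extra share |
|---|---|---|
| 38% | 50% | 24% |
| 34% | 50% | 32% |
| 42% | 50% | 16% |
| 38% | 44% | 14% |

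**Who the extra conceivers might be.** Let p be the share of women metabolically healthy at baseline. The protocol does not give it, so assume 30% to 60%. The rate in the other women is then (38 − 52p)/(1 − p). Assume also that the whole gain to 50% falls on them; their rate must then reach (50 − 52p)/(1 − p).

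| p | Unhealthy women: S-PRESTO rate → rate needed | Unhealthy share of pregnancies: S-PRESTO → HELMS |
|---|---|---|
| 0.3 | 32.0% → 49.1% | 58.9% → 68.8% |
| 0.5 | 24.0% → 48.0% | 31.6% → 48.0% |
| 0.6 | 17.0% → 47.0% | 17.9% → 37.6% |

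Under these assumptions, case mix shifts by about 10 to 20 points towards women unhealthy at baseline.

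**Effect on the contrast.** Let k be the underlying risk of extra conceivers relative to women who would conceive anyway, and apply the true risk ratio to every HELMS pregnancy. Then apparent RR = true RR × (0.76 + 0.24k). The protocol gives no k, so it is varied. With a true RR of 0.90:

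| k | 0.76 + 0.24k | Apparent RR |
|---|---|---|
| 0.75 | 0.94 | 0.85 |
| 1 | 1.00 | 0.90 |
| 1.25 | 1.06 | 0.95 |
| 1.5 | 1.12 | 1.01 |
| 2 | 1.24 | 1.12 |

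Below k = 1 the bias favours HELMS. Above it the bias works against HELMS, and from about k = 1.5 it cancels a true 10% reduction.

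**The case against.** **The denominator and covariates can be left to the analysis plan.** This largely stands: the article fixes no denominator, and its confounder list is open, so BMI and metabolic status are not excluded. But for obstetric, delivery, fetal and neonatal outcomes a woman who did not conceive has no value, so the named outcomes settle the analysis set. The stated adjustment is aimed at confounding and commits to nothing on selection by conception.

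**The direction is not established.** This stands. A reader might infer that success on conception must make HELMS pregnancies look worse, so that a real benefit would appear as harm. The 52% against 38% contrast suggests that direction but does not prove it. No passage says that the gain falls wholly on metabolically unhealthy women, and at p = 0.6 their rate would have to rise nearly threefold. The article also treats conception as the end result of better metabolic and mental health, so a woman unhealthy at baseline need not be at high risk when she conceives. Nor can the 15% pregnancy loss supply a size: it is the planned rate for HELMS pregnancies, not an S-PRESTO rate, and no loss rate is given for extra conceivers.

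**The bias may be small beside sampling error.** Partly stands. With no true effect, the bias in percentage points is 0.24 times the risk gap between extra and other conceivers. For a risk near 15% in 200 pregnancies, the 95% half-width for HELMS alone is 1.96 × √(0.15 × 0.85/200), about 5 points. A bias of that size needs a gap of 5/0.24, about 21 points.

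**A per-woman analysis is not simply better.** This stands. It does not suit continuous outcomes such as infant weight, and it can hide harm. If complications rose from 20% to 35% of pregnancies, complication-free pregnancies per 100 women would still rise from 38 × 0.80 = 30.4 to 50 × 0.65 = 32.5, ignoring losses.

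**A reader might also infer that no S-PRESTO comparison escapes the problem.** That goes too far, because live birth can be compared per woman entering the preconception phase.

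**Conclusion.** The concern holds in limited form. For outcomes that exist only after conception, the HELMS versus S-PRESTO contrast conditions on an event that the intervention is expected to change, and it should not be read alone as an intervention effect. The 24% is a planning figure: it requires the expected 50% to be reached, HELMS women to share the 38% untreated rate, and no conceptions to be prevented. Bias against HELMS is plausible from the S-PRESTO rates by metabolic profile, but bias in its favour is also possible, and the size rests on a relative risk that the protocol does not give. The comparison is supplementary, S-PRESTO is a historical cohort rather than a control arm, and the Discussion presents the trial as preliminary evidence. The point is therefore a cheap improvement to a secondary analysis.

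**What to change.** In Planned analyses:

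1. Commit to adjusting the per-pregnancy HELMS versus S-PRESTO contrasts for preconception BMI and baseline metabolic status (metabolic syndrome or insulin resistance), or standardising to them, in addition to age, ethnicity and education.
2. For binary outcomes, report beside these a contrast per woman entering the preconception phase: live birth, and live birth without the complication in question. Women who do not conceive count as not having the event in both cohorts. This accompanies the per-pregnancy results and does not replace them.
3. State that the per-pregnancy contrasts condition on conception and are not to be read alone as benefit or harm of the intervention.

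The cost is a little wording and analysis. HELMS already takes the metabolic measurements at its preconception baseline visit, and S-PRESTO evidently holds them, since the protocol quotes its pregnancy rate by metabolic profile. Adjustment reduces the bias but does not remove it if unmeasured determinants of conception also affect pregnancy risk. The per-woman figures mix conception with pregnancy outcome, so the two sets must be read together.
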